#### Kidney size

The size of the kidney supplied by the renal artery that determined the patient's eligibility for the study will be measured by renal duplex sonography at baseline and after 6 and 12 months.

#### Evaluation of anti-hypertensive medication

All medication of the patients will be recorded in the CRFs and any changes in the medication must be recorded. Per patient antihypertensive medication will be analysed according to total number of anti-hypertensive medications, drug name, drug class, daily dose and regimen. Change in medical treatment will be compared with regard to anti-hypertensive medication using the classification of WHO daily defined doses (DDD). Total amount of anti-hypertensive medication recorded at different time points will be calculated according to the following formula:

Dose per day/DDD for this drug

Anti-hypertensive medication for each patient at baseline, 2, 6 and 12 months will be compared to the medication taken before randomisation.

#### Classification of heart failure

Heart failure will be classified according to the classification of the New York Heart Association at baseline, 2, 6 and 12 months.

#### Quality of Life assessment

During the study the quality of life will be assessed at baseline, 6 and 12 months using a validated questionnaire [28] (SF-12v2™) established to measure the impact of disease on the patients' quality of life. It has been used extensively as a screening tool, and is frequently used as part of longer, condition-specific surveys. Questionnaires will be supplied in the validated version of local language(s) of each participating country.

#### Patient survival

Patient survival will be calculated after the last follow-up has been completed as percentage of patients still alive and followed-up compared to treated/randomised patients.

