**Figure 1 F1:**
[figure not shown]
**Study profile**.

Serum Creatinine (SCr) values and eGFR will be assessed from patient's medical files after obtaining informed consent, and a blood sample for determination of the baseline value will be obtained. At time of randomisation the patient's medical history and concomitant medication, clinical events and quality of life will be recorded. A 24 hour ambulatory blood pressure measurement will be obtained. Renal stenting will be performed under angiography imaging. For patients randomised to best medical treatment the degree of stenosis measured by renal duplex sonography will be confirmed by MR angiogram or multi-slice CT where possible. Best medical treatment will be initiated at randomisation or post procedurally (for PTRAS arm only), and adjusted as needed at all visits. For all patients renal duplex sonography will be performed at baseline, post procedure (for PTRAS arm only), and at 6 and 12 months follow up. Clinical events will be obtained at baseline and during all visits including a telephone follow up 3 years after randomisation. Twenty four hour ambulatory blood pressure measurement and blood sampling for eGFR determination will be done at baseline, post procedure (for PTRAS arm only), and after 2, 6 and 12 months. Adverse events and concomitant medication will be recorded up to 12 months after randomisation. At baseline, 6 and 12 months patients' quality of life will be assessed using a validated general health quality instrument (SF-12v2™). For further assessments see flow chart and table of events. Patients randomised to the 'no revascularisation'-group and presenting with a severe increase in serum creatinine concentration indicating the need of renal replacement therapy, or recurrent flash pulmonary oedema despite existing multidrug therapy (5 drugs), may receive a Dynamic Renal stent.

Only patients who have given written informed consent in accordance with the applicable regulations, the Declaration of Helsinki, GCP and ISO 14155 will be enrolled in the trial. The trial is conducted in compliance with the Declaration of Helsinki. The trial was approved by the central ethics commission "Ethik-Komission der Albert-Ludwigs-Universität Freiburg", Freiburg, Germany

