• Left ventricular mass index (LVMI) calculated from echocardiography or cardiac magnet resonance imaging at baseline and 12 months. The LVMI [g/m^2^] is defined as left ventricular mass divided by body surface area [m^2^]. Left ventricular mass is calculated by using the method described by Devereux and Reichek [21], or as supplied by the manufacturer of the echo device.

• Difference in the size of kidney (pole to pole length) at baseline, 6 and 12 months measured by renal duplex sonography.

• Total number, drug name, drug class, daily dose, regimen and Defined Daily Dose (DDD), of anti-hypertensive drugs at baseline, 2, 6 and 12 months.

• Change in anti-hypertensive therapy at 2, 6 and 12 months.

• Classification of heart failure according to the New York Heart Association (NYHA) at baseline, 2, 6 and 12 months.

• Change in NYHA classification of heart failure at 2, 6 and 12 months.

• Quality of life at baseline, 6 and 12 months (i.e. SF-12v2™).

• Change in quality of life at 6 and 12 months.

• Patient survival

• Laboratory parameters at baseline, 2, 6 and 12 months (blood), or baseline and 12 months (urine).

• Adverse events.

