##### Calculations

The sample size (N) has been calculated using the methods of Bock J, 1998 [22] and Chow

SC, 2003 [23], N = nT + nC. 4 (u1.α/2 + u1.β)2 (σ/Δ)2 for σC 2 = σT 2 = σ2

The probability for incorrect rejection of H0 for a two-sided test (α/2 = 0.025) is u1-0.025 = 1.9600.

The probability for correct rejection of H0 (1-β = 80%) is u0.8 = 0.8416.

Based on published data [24], the estimated GFR difference between baseline and 12 month follow-up in patients with unilateral RAS>70% is 4.35 ml/min. Moreover, from the DRASTIC study [25] considering the patient population with bilateral stenosis the estimated GFR difference at 12 months was 10.0 ± 16 ml/min. Furthermore, in a usual patient population the proportion of patients with bilateral RAS is 15% to 20%. This leads to a calculated increase of estimated ΔGFR for a mixed cohort of patients with unilateral and/or bilateral RAS of approximately: ΔeGFR = 0.2*10+0.8*4.35 ≈ 5.5 ml/min μ_T _= 5.5 ml/min.

In addition, for the medication group, we can assume an eGFR difference or decrease of

μ_C _= -1.0 ml/min at 12 months follow up.

The relevance level is assumed to be 20% of the difference between the therapy and medication or control group. Therefore, the sample size can be calculated as shown in Table 1.

**Table 1 T1:** Calculation of sample size

**Expectation value**			**Relev**.	**Variance^1/2^**			**Sig. level**	**Statistical**	**Sample**
			
**Therapy**	**Ref**.	**Min. diff**.	**level**	**Therapy**	**Ref**.	**k **=	**1-sided**	**power**	**size**
**mue_T_**	**mue_C_**	**Delta**	**delta**	**sigma_T_**	**sigma_C_**	**n_T_/n_C_**	**alpha = 0.05**	**1-beta**	**N = n_T_+ n_C_**

5.5	-1.0	6.5	2.0	14.0	14.0	1.50	1	0.80	**250**

Considering a drop-out rate of approximately 20%, and a PTRAS rate of 20% of patients being initially randomised to BMT group, a total of 300 patients will be enrolled, 150 patients per group. A study patient that has been withdrawn from the study will not be replaced. It is intended to include between 6 and 24 patients per centre.

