Renal function is one of the most powerful predictors of survival [40]. Another one is left ventricular hypertrophy [41]; the analysis of the course of left ventricular mass index is also included as a secondary endpoint because the reducing the activation of the renin-angiotensin-aldosterone-system by RAS revascularisation should lead to a regression of left ventricular hypertrophy [41]. Affecting these major endpoints, renal function and left ventricular hypertrophy, RAS stenting should also impact the composite clinical endpoint of patient survival, hospitalisation and end-stage renal failure after 3 years.

Provided a timely initiation of all study sites it is expected to finish patient enrolment within 1 year so that the analysis of the primary endpoint should be available in 2011.

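### The stated survival percentage counts a living patient who is lost to follow-up as a non-survivor, and leaves its denominator loosely worded

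*Protocol article*

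**What the plan says.** The Endpoints section lists "Patient survival" among the secondary endpoints, with no time point or method. The Patient survival section supplies the rule: "Patient survival will be calculated after the last follow-up has been completed", as the "percentage of patients still alive and followed-up compared to treated/randomised patients". The last follow-up is at 3 years; under Figure 1 in Study design, clinical events are collected at baseline and at all visits, "including a telephone follow up 3 years after randomisation".

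The Statistical Analyses section puts all patients on an intent-to-treat basis, then says that the data analysis covers patients who meet the eligibility requirements. It names percentages, a binomial test for proportions, and a t-test or rank tests for metric data. It names no method that handles censoring. What it expressly leaves to the statistical analysis plan is other subgroup analyses.

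**The concern.** The numerator sets two conditions, being alive and being followed up; the denominator sets only one, having been treated or randomised. The result mixes mortality with completeness of follow-up. Two groups with the same mortality but different success in tracing patients would show different survival.

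The slash in the denominator adds a second, smaller problem. Treated and randomised patients need not be the same set, and the sentence does not choose between them.

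At stake is the reading of one secondary endpoint. The Discussion gives mortality some weight, since it expects that "RAS stenting should also impact the composite clinical endpoint of patient survival, hospitalisation and end-stage renal failure after 3 years". That remark concerns a composite and does not use the survival formula, so it shows only that survival is of interest.

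**Working it through.** The documents state no survival rate, number of deaths or power for survival, so there is no figure of the plan to reproduce. The check works out what the stated formula returns.

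**Inputs from the protocol article**
- Numerator and denominator: Patient survival section.
- Group size: "a total of 300 patients will be enrolled, 150 patients per group" (Calculations).

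**Inputs that are assumptions**
- S, true survival at the last follow-up.
- d, the proportion with unknown status at the last follow-up, independent of death.
- The number treated.

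**Step 1. Level.** With all randomised patients as denominator, the formula returns the proportion both alive and followed up. If loss is independent of death, this is S × (1 − d). For S = 85%:
- d = 5%: 0.85 × 0.95 = 80.75%
- d = 10%: 0.85 × 0.90 = 76.5%
- d = 20%: 0.85 × 0.80 = 68%
- d = 30%: 0.85 × 0.70 = 59.5%

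The shortfall is S × d, which is zero only if no living patient is lost.

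**Step 2. Equal loss in both arms.** Take true survival of 80% and 90% and d = 20% in each arm. The report is 0.80 × 0.80 = 64% and 0.90 × 0.80 = 72%, so 10 points shrink to 8. If the two percentages were compared at two-sided 5%, with n per arm:

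power = Φ[(|p1 − p2| − 1.96 × SE0) / SE1], where SE0 = √(2p̄(1 − p̄)/n) and SE1 = √((p1(1 − p1) + p2(1 − p2))/n).

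- 64% v 72%, n = 150: SE0 = 0.0539, SE1 = 0.0537, power 32%.
- 80% v 90%, n = 120 (only those with known status, 150 × 0.80): SE0 = 0.0461, SE1 = 0.0456, power 58%.
- 80% v 90%, n = 150 (complete follow-up): power 68%.

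With no true difference, both arms report the same percentage and the rejection rate stays at 5%.

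**Step 3. Unequal loss, no true difference.** With S = 85% in both arms, the apparent difference is 0.85 × (d2 − d1). Rejection rates use the same approximation, n = 150 per arm:
- 17.5% v 22.5% loss: 4.25 points, rejection 12%
- 15% v 25% loss: 8.5 points, rejection 35%
- 10% v 30% loss: 17 points, rejection 89%

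None of these loss rates comes from the documents. They show how sensitive the formula is, not what to expect.

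**Step 4. Denominator.** At S = 85% and d = 20%, 150 × 0.68 = 102 patients are alive and followed up. Of 150 randomised that is 68.0%; of an assumed 135 treated it is 102/135 = 75.6%.

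**The case against.** Much can be said for the plan, and several stronger readings that a reader might infer do not stand.

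- **That vital status rests on one telephone call.** It does not. Clinical events, including renal and cardiac death, are collected at 2, 6 and 12 months as well as 3 years (Endpoints). Deaths must be reported within 24 hours (Serious Adverse Event), and the committees rule on every death (Study Committees). Only after month 12 is the telephone contact the sole scheduled one.
- **That one patient in five will be miscounted.** The Calculations section does say "Considering a drop-out rate of approximately 20%, and a PTRAS rate of 20% of patients being initially randomised to BMT group", but this allowance supports the sample size. The Patient population section ties the 300 enrolled to at least 250 with a valid primary endpoint, which is a 12-month eGFR. A patient without that value may still be reached at 3 years, and early deaths may already be within the 20%.
- **That the survival comparison between arms is therefore wrong.** The section gives a percentage and assigns no between-arm test to it. Equal, non-informative loss creates no false difference. Unequal loss is conceivable in a stent-versus-medication trial, but no section gives loss by arm or its direction.
- **That the denominator is open.** The intent-to-treat sentence largely settles it in favour of randomised patients, although the restriction to eligible patients in the next sentence and the slash itself leave loose ends.

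It can also be said that a condensed article leaves time-to-event methods to the statistical analysis plan. That would answer a complaint that a method is missing. Here the article states a rule, and nothing shown withdraws it. The objections limit the size of the point; none repairs the formula.

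**Conclusion.** The point holds in limited form. The stated rule treats a living patient with incomplete follow-up as a non-survivor. With all randomised patients as denominator, the percentage is too low by S × d if loss is independent of death: 4.25 points at 5% loss and 8.5 points at 10%, for an assumed true survival of 85%. The direction of this error follows from the wording; its size rests on S and 3-year loss, which the documents do not give.

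For a comparison of the arms, a true difference is diluted under equal, non-informative loss. A spurious difference arises only under unequal or informative loss, so the documents do not support calling the comparison biased as a matter of fact. The denominator wording is a clarification. The primary endpoint and the sample size are untouched, so the change is worth making but not critical.

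**What to change.** Replace the sentence in the Patient survival section with: *Survival is estimated by Kaplan-Meier from randomisation in all randomised patients by assigned arm, censored at the last date known alive, with loss to follow-up reported separately by arm.* This also removes treated patients as a possible denominator, in line with the intent-to-treat statement.

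Do not carry plain Kaplan-Meier over to the clinical-event endpoints with cause-specific components (renal or cardiac death, dialysis, revascularisation). Death from other causes is a competing event there, and censoring it would overstate their incidence.

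The cost is small. Deaths are already reported and reviewed; the date of last contact must be recorded for every patient. Kaplan-Meier still assumes that loss is non-informative, which is why loss by arm should be shown beside it.

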#### Evaluation of safety

The safety of the Dynamic Renal stent will be analysed by adverse events and device related adverse events.

### Statistical Analyses

All patients will be analysed on an intent-to-treat basis. Data analysis will be performed on all patients who meet the eligibility requirements of this study using descriptive methods. Discrete variables will be presented as counts and percentage of the total. Continuous variables will be presented as mean ± standard deviation. In case of relative likelihoods the exact one-sided confidence interval of 95% will be calculated.

For the confirmatory analysis of relative likelihoods a binominal test will be performed. For the confirmatory analysis of metric data a t-Test will be performed. If a Kolmogorov-Smirnov-Test shows the data are not normally distributed, a non-parametric Wilcoxon-Test or in case of an inter-individual comparison of 2 datasets a Mann-Whitney-U-Test will be performed.

It is intended to perform the following sub analyses:

- Analysis by treated lesion,

- Analysis including time points after receipt of the Dynamic Renal stent during the study from patients initially randomised to the no revascularisation group.

Other subgroup analyses will be specified in the statistical analysis plan.

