### Endpoints

*Primary Endpoint*: The primary endpoint is the difference between treatments in change of eGFR over 12 months.

*Secondary Endpoints*: Secondary endpoints are defined as:

• Change in eGFR at 2, 6 and 12 months.

• Difference between treatments in change of eGFR over 2 and 6 months.

• Difference in eGFR slope between pre-treatment and post treatment time points at 2, 6 and 12 months.

• Change of renal function based on the eGFR slope change between pre-treatment and post-treatment at 2, 6 and 12 months (i.e. improvement, stabilisation, failure).

• Ratio of average Resistance Index (RI) at baseline, 6 and 12 months. Intra-renal Resistance Index is defined and calculated by the following formula: Intra-renal RI = (Peak Systolic Velocity-End Diastolic Velocity)/Peak Systolic Velocity.

• Degree of restenosis at 6 and 12 months.

• Clinical events overall: renal or cardiac death, stroke, myocardial infarction, hospitalisation for congestive heart failure, progressive renal insufficiency (i.e. need for dialysis), need for permanent renal replacement therapy, and need of target vessel revascularisation (TVR) or target lesion revascularisation (TLR) at 2, 6 and 12 months, and 3 years.

• Clinical events renal: renal death according to ICD 10, progressive renal insufficiency (i.e. need for dialysis), need for permanent renal replacement therapy, and need of TVR or TLR at 2, 6 and 12 months, and 3 years.

• MACCE: cardiac death, stroke, myocardial infarction, hospitalisation for congestive heart failure at 2, 6 and 12 months, and 3 years.

• Technical success, defined as successful access and deployment of the device with appropriate lesion coverage, stent positioning and patency determined by angiography.

• Acute procedural success, defined as residual percent diameter stenosis <30% by quantitative computerised angiography.

• Procedural success, defined as successful lesion crossing and stent positioning without the occurrence of a serious adverse event up to the moment the introducer sheath is removed,

• Average systolic and diastolic blood pressure (i.e. ambulatory 24 h-BP) at baseline, post procedure, 2, 6 and 12 months.

• Change in average systolic and diastolic blood pressure (i.e. ambulatory 24 h-blood pressure monitoring) at 2, 6 and 12 months.

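### The methods stated for clinical events to 3 years take no account of follow-up time, so rates are understated if lost patients stay in the denominator, and a binomial test does not compare two arms

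*Protocol article*

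**What the plan says.** The Endpoints section defines three clinical-event composites (overall, renal and MACCE), each read at four times. The overall and renal lists both end "and need of target vessel revascularisation (TVR) or target lesion revascularisation (TLR) at 2, 6 and 12 months, and 3 years", and the third reads "MACCE: cardiac death, stroke, myocardial infarction, hospitalisation for congestive heart failure at 2, 6 and 12 months, and 3 years". The Study design text after Figure 1 says how they are collected: "Clinical events will be obtained at baseline and during all visits including a telephone follow up 3 years after randomisation".

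The methods for such data are all in Statistical Analyses. Presentation: "Discrete variables will be presented as counts and percentage of the total". Interval: "In case of relative likelihoods the exact one-sided confidence interval of 95% will be calculated". Test: "For the confirmatory analysis of relative likelihoods a binominal test will be performed". Analysis set: "All patients will be analysed on an intent-to-treat basis". The article names no time-to-event method and no censoring rule. The only matter this section leaves to the statistical analysis plan is further subgroup analyses.

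The expected loss is given under Calculations, in sizing the 12-month eGFR endpoint: "Considering a drop-out rate of approximately 20%, and a PTRAS rate of 20% of patients being initially randomised to BMT group". Withdrawn patients are not replaced.

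**The concern.** A cumulative 3-year event needs three years of observation to be ruled out. A patient lost at month 4 can contribute an event for 4 months. If that patient stays in the denominator, the other 32 months are scored as event-free. Leaving such patients out altogether instead discards events already seen. Neither percentage uses the event or loss dates.

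The composites are the trial's hard outcomes, and the Discussion expects stenting to affect a clinical composite at 3 years. Understated rates would misdescribe risk in both arms. If loss differs between arms, the arm with more loss looks better. One arm has a procedure and the other does not, so unequal retention is plausible.

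The test raises a second issue. A binomial test sets one proportion against a fixed value, and the exact one-sided interval is likewise a single-proportion method. No fixed value is given for the composites, where the question is a difference between randomised arms.

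**Working it through.** **Inputs.** The plan states no event rate and no power for clinical events, so there is no event figure of its own to reproduce. From the documents: drop-out about 20%; 300 enrolled to give 250 with a valid primary endpoint, that is 50/300 = 16.7% without one; 150 per group; horizon 36 months. Assumed: constant hazard, no contact after loss, loss unrelated to risk, and 3-year risks of 5% to 50%.

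**Formula.** With true 3-year risk p and fraction lost d:

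crude rate = (1 − d) × p + d × (mean risk accrued before loss); shortfall = 1 − crude/p.

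**Worked case.** Hazard 0.10 per year, 20% lost evenly over year 1:
- True risk: 1 − exp(−0.3) = 25.9%.
- Mean risk before loss: 1 − (1 − exp(−0.1))/0.1 = 4.8%.
- Crude rate: 0.8 × 25.9 + 0.2 × 4.8 = 21.7%.
- Shortfall: 1 − 21.7/25.9 = 16%.

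**Timing of the loss.** 3-year shortfall for risks from 5% to 50%:

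| When patients are lost | 20% lost | 16.7% lost |
|---|---|---|
| All at day 0 | 20.0% | 16.7% |
| Evenly over months 0–12 | 16.6% to 15.7% | 13.8% to 13.1% |
| All at month 12 | 13.2% to 11.7% | 11.0% to 9.8% |
| Evenly over months 0–36 | 9.9% to 8.9% | 8.3% to 7.4% |

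If loss continued at 20% per year for three years, the shortfall would be 26.7% to 25.0% (3-year risks of 10% to 40%).

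**Earlier time points.** With 20% lost evenly over year 1, the share of observation time missing by month t is half the fraction lost by then:
- 2 months: 0.2 × (2/12)/2 = 1.7%.
- 6 months: 0.2 × (6/12)/2 = 5%.
- 12 months: 0.2/2 = 10%. The exact shortfall is 9.8% to 9.6% for 12-month risks of 10% to 20%.

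**Comparison of arms.** Same hazard in both arms, loss evenly over year 1:
- 15% lost: 0.85 × 25.92 + 0.15 × 4.84 = 22.8%.
- 25% lost: 0.75 × 25.92 + 0.25 × 4.84 = 20.6%.
- Ratio: 20.6/22.8 = about 0.91, with no true effect.

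With equal loss, both arms shrink by nearly the same factor. The risk ratio is then almost unbiased, and the risk difference shrinks.

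**Binomial test.** Suppose the observed control proportion (n = 150) were used as the fixed null value. The test would count p(1 − p)/n as the variance of the difference, whose true value is twice that. Type I error at a nominal two-sided 5% is then 2[1 − Φ(1.96/√2)] = 2[1 − Φ(1.386)] = 16.6%. Simulation with 150 per arm gave 16.6%, 15.8% and 14.9% at p = 0.10, 0.25 and 0.50.

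**The case against.** The presentation sentence is a generic line about all discrete variables. It does not define the denominator for 3-year events and nowhere says that a drop-out counts as event-free. The Patient survival section in fact works the other way: a lost patient is not among those alive and followed up, so loss lowers survival. Denominators and censoring rules are commonly left to a statistical analysis plan, and this is a condensed article. These points make the denominator an inference. They do not remove the concern, because the article does more than stay silent: it states a percentage and a test, and neither uses follow-up time.

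A reader might infer that event rates come out 16% too low on the plan's own drop-out. The documents do not support that. The 20% belongs to the 12-month eGFR sizing, its timing is not given, and a patient without a valid 12-month eGFR may still answer the 3-year call. Events are also not learned only at planned contacts: serious adverse events and deaths go to the sponsor within 24 hours of the investigator learning of them, and the DSMB/CEC rules on all deaths. Where such reports still arrive after loss, the shortfall is smaller.

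A reader might also infer that the plan's test has a 15% to 17% type I error. That figure applies only if the observed control rate is inserted as a known constant, which the plan does not say. Technical, acute procedural and procedural success are true single-arm proportions, for which the binomial test and one-sided interval are suitable.

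Finally, bias between arms needs unequal loss, and the 15% and 25% used here are illustrations. All of this limits the size and certainty of the point. None of it makes the stated methods suitable for comparing arms on cumulative 3-year events.

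**Conclusion.** The point holds in conditional form. If the total is all randomised patients, as intent-to-treat suggests, the stated methods understate event rates. For a total loss of 20%, the 3-year shortfall is about 9% to 20% depending on timing, about 16% being the case of even loss over year 1. The 12-month shortfall is about 10% for even loss. These figures rest on a constant hazard and no contact after loss; ongoing loss would enlarge them, and continued event reporting would reduce them.

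The risk ratio is nearly unbiased under equal loss. Loss of 15% against 25% would give a spurious ratio of about 0.91. Separately, the article names no two-sample method for comparing proportions. If the control rate were treated as fixed, type I error would be about 15% to 17%. The affected endpoints are secondary; the primary eGFR analysis is not touched.

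**What to change.** In Statistical Analyses, state that the overall, renal and MACCE composites and their component events are analysed as time from randomisation to first event, censored at last contact. Report cumulative incidence at 2, 6, 12 and 36 months, with deaths outside the composite as a competing event. Compare randomised arms with a log-rank test or Cox model and give two-sided 95% intervals.

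For outcomes that are binary at one visit, compare arms with Fisher's exact or a chi-square test and a two-sided interval for the difference, and show the number missing by arm. Keep the one-sample binomial method for technical and procedural success.

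The cost is wording and some programming, with no added patients or visits. The CRF already records the onset date of adverse events, and the DSMB/CEC classifies all clinical events. Two limits remain. The Study design text has adverse events recorded only to 12 months, so later event dates would rest on serious adverse event reports and the 3-year telephone contact and may be approximate. Censoring also still assumes that loss is unrelated to risk, so it does not cure informative loss that differs by arm.

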### Sample Size Calculation, Statistics, and Calculations

#### Sample Size Calculation

The primary endpoint is the difference between treatments in change of eGFR over 12 month. For this endpoint the intention-to-treat population (ITT) will be taken for primary analysis.

Definitions:

• Controls expectation value μ_C_, variance σ_C _^2 ^and group size n_C _= Medication

• Treatment expectation value μ_T_, variance σ_T _^2 ^and group size n_T _= Medication and Stent

A two-sided test will be performed.

• Null hypothesis: H_0_: μ_T _= μ_C_

• Alternative hypothesis: H_A_: μ_T _≅. μ_C _(↔.μ_T _< μ_C _or μ_T _> μ_C_)

• Minimum difference: Δ = μ_T _- μ_C_

• Variances: σ_T _^2 ^and σ_C _^2^

• Level of significance: α

• Statistical power: 1 - β

• Sample size: N = n_T _+ n_C_

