#### Clinical events

Clinical events will be analysed for:

• Overall combined events (i.e. renal or cardiac death, stroke, myocardial infarction, hospitalisation for congestive heart failure, progressive renal insufficiency (i.e. need for dialysis), need for permanent renal replacement therapy, and need of TVR or TLR),

• renal clinical events (i.e.,. renal death defined as patient death classified according to the *International Classification of Disease*, *Tenth _Revision *(ICD-10) codes N00-N07, N17-

N19, and N25-N27, progressive renal insufficiency (i.e. need for dialysis), need for permanent renal replacement therapy, and need of TVR or TLR),

• MACCE (i.e. cardiac death, stroke, myocardial infarction, hospitalisation for congestive heart failure),

• individual events.

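### A blanket one-sided 95% interval, with no direction named, is prescribed for all proportions, although the text sets a two-sided test and most binary outcomes are reported in both arms

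*Protocol article*

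**What the plan says.** Under Statistical Analyses, the first paragraph describes analysis "using descriptive methods": counts and percentages, then means with standard deviations. It closes with the rule for proportions: "In case of relative likelihoods the exact one-sided confidence interval of 95% will be calculated". The term relative likelihoods is not defined. I read it as proportions, because the same section contrasts it with metric data. The next paragraph gives the test: "For the confirmatory analysis of relative likelihoods a binominal test will be performed". Neither paragraph names a direction for the interval, a list of endpoints to which it applies, or an interval for a difference between arms. The only item that the section defers to the statistical analysis plan is the set of further subgroup analyses.

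On sidedness, the Sample Size Calculation section says "A two-sided test will be performed" and writes the alternative hypothesis in both directions. Calculations then uses α/2 = 0.025 with the normal quantile 1.9600. The significance column of Table 1, however, is headed 1-sided with alpha = 0.05.

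The proportions in scope include the composites listed where the article says "Clinical events will be analysed for" (overall, renal and MACCE), the renal-function categories, the blood-pressure categories and the survival percentage. All of these arise in both arms. Technical and procedural success arise in the stent arm only.

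**The concern.** A one-sided interval answers a question with a known direction, for example whether device success is at least some value. For event rates in a randomised comparison of stenting with medical treatment, the direction is not known in advance. The article's Background itself says that angioplasty can worsen renal function. A reader of the results needs to see how low and how high each rate could plausibly be.

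The rule creates three problems:

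- **One bound is missing.** The interval runs to 0% or to 100% on the side that is not reported.
- **The direction is open.** With nothing fixed, it could be chosen endpoint by endpoint after the data are seen.
- **The tail error does not match the text.** A one-sided 95% limit puts 0.05 in one tail. The sample-size text uses 0.025 per tail for the primary comparison.

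The stake is the readability and consistency of the secondary binary results, not the primary conclusion.

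**Working it through.** **Inputs.** The confidence level and the one-sided exact form come from Statistical Analyses. The 150 patients per arm come from Calculations. The article gives no event rates, so 10% (15/150) and 20% (30/150) are assumptions, with 2% and 50% added to show the range.

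**1. Sidedness in the article.** The general formula is N = [(1+k)²/k] × [(u_α + u_β) × σ/d]², with σ = 14 and u_β = 0.8416.

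- Table 1 as printed, taking d = 6.5 − 2.0 = 4.5, k = 1.5 and a one-sided 0.05 (u_α = 1.6449): (6.25/1.5) × (2.4865 × 14/4.5)² = 249.3, or 100 + 150 = 250 after rounding up. This matches the stated 250.
- Text version, two-sided (u_α = 1.9600) with 1:1 allocation: 4 × (2.8016 × 14/6.5)² = 145.6 at d = 6.5, and 303.9 at d = 4.5. Neither gives 250.
- A two-sided test with d = 5.0 would give 246 (k = 1) or 256 (k = 1.5), but a difference of 5.0 is not stated anywhere.

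Subtracting the relevance level is my reading of the table. In the text at hand the entry under the significance header is 1, so the table may be misaligned. What can safely be said is that the text is two-sided, the table header is one-sided, and the stated total matches the one-sided reading. The article is inconsistent on sidedness.

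**2. Exact (Clopper-Pearson) limits.** For x events in n patients and tail error a, the lower limit is the a-quantile of Beta(x, n−x+1) and the upper limit is the (1−a)-quantile of Beta(x+1, n−x). The one-sided 95% limit uses a = 0.05 and the two-sided 95% interval uses a = 0.025 in each tail. Because a two-sided 90% interval also uses a = 0.05 per tail, its limits coincide with the one-sided 95% limits.

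| Events/n | One-sided 95%: lower *or* upper | Two-sided 95%: lower *and* upper | Shift, lower / upper (points) |
|---|---|---|---|
| 3/150 | 0.55% or 5.09% | 0.41% to 5.73% | 0.14 / 0.64 |
| 15/150 | 6.27% or 14.98% | 5.71% to 15.96% | 0.56 / 0.98 |
| 30/150 | 14.78% or 26.13% | 13.92% to 27.30% | 0.86 / 1.17 |
| 75/150 | 43.0% or 57.0% | 41.74% to 58.26% | 1.3 / 1.3 |

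With 125 per arm (half of the 250 patients expected to have a valid primary endpoint) the picture is the same. For 25/125 the one-sided limits are 14.30% or 26.80%, against 13.38% to 28.09%, which are shifts of 0.92 and 1.29 points.

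**3. What a between-arm interval would show.** Assume 30/150 against 15/150, a difference of 10.0 points. The Wilson 95% limits are 14.38% to 27.11% and 6.15% to 15.84%. Newcombe's method gives:

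- lower limit: 10.0 − √[(20.0 − 14.38)² + (15.84 − 10.0)²] = 10.0 − 8.1 = 1.9 points
- upper limit: 10.0 + √[(27.11 − 20.0)² + (10.0 − 6.15)²] = 10.0 + 8.1 = 18.1 points

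Two one-sided limits, one per arm, do not yield this range.

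**The case against.** The strongest case for leaving the sentence alone has five parts.

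- **It is descriptive.** The sentence ends a descriptive paragraph, no decision rule depends on the interval, and no benchmark proportion is given against which a limit would be tested. This stands, and it limits the consequence to reporting.
- **The two-sided statement belongs to the primary endpoint.** The hypotheses concern mean eGFR change, and nothing in the article sets two-sided error control for the binary secondary endpoints. Table 1 is itself headed one-sided. This stands too: the trial cannot be called two-sided throughout, and the mismatch is with the text, not with a settled design. It does not justify an interval without a direction.
- **The effect on the limits is small.** It is about one percentage point under assumed rates. That is correct. The open side and the unstated direction matter more than the shift.
- **A one-sided bound suits single-arm device performance.** For technical and procedural success it is defensible. Only the missing direction is a fair criticism there.
- **The analysis plan is not shown.** A reader might infer that the trial will never report an interval for the difference between arms. The article does not say so. It leaves the quantity undefined, and the statistical analysis plan may supply such an interval. The supportable statement is only that none is named in this section. The one-sided rule itself is different: the article fixes it, so it is not a detail left for later.

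A reader might also infer that these are really 90% intervals. They are not. An exact one-sided 95% interval has at least 95% coverage, and only its one finite limit coincides with a limit of the two-sided 90% interval. It would become a 90% interval only if both limits were printed together.

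**Conclusion.** The point holds in a limited form. The article prescribes a one-sided 95% interval for all proportions, without direction or exception. That suits neither outcomes reported in both arms nor the two-sided test set in the sample-size text. At the assumed 10% and 20% event rates with 150 per arm, the finite limit is about 0.6 to 1.2 points tighter than a two-sided 95% limit, and the other limit is not given.

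This rests on reading relative likelihoods as proportions and on assumed event rates. It does not extend to the primary endpoint, which is a change in eGFR analysed as a continuous variable, and it does not show that any conclusion of the trial would change. The correction is worth making because the rule is explicit and costs almost nothing to repair, but it is not critical to the trial.

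**What to change.** Replace the sentence with a rule along these lines: each proportion will be given per arm with a two-sided exact 95% confidence interval; for binary endpoints compared between arms, the risk difference will be given with a two-sided 95% confidence interval (Newcombe or Miettinen-Nurminen, one of them named in advance). If a one-sided bound is kept for technical or procedural success in the stent arm, state which limit is reported. Define relative likelihoods, or use the word proportions, and bring the Table 1 header into line with the sample-size text on sidedness.

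The change needs no new data and no more patients. The cost is slightly wider limits, by roughly one percentage point in the examples above.
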